## 13.6 Resource use and costs

To specifically inform the health economic analyses (see section 17), we will utilise the trial to gather data on the resources required for:

- Audit data collection and submission (time of hospital personnel recorded for a sub-sample). This will be facilitated by requesting data collectors at a small sample of Trusts / Health Boards to record (on the NCA proforma described in section 13.3 above) their job title and the time taken to extract the required audit data from patient case notes and hospital information systems. So as not to burden trial sites, the time taken to enter the data onto the NCA system will be estimated by having trial personnel enter data for a number of 'mock' audit cases.
- Development and delivery of standard and enhanced feedback documents (time of NCA personnel in designing and populating documents with audit data). The resources required to design and populate the standard and enhanced versions of the feedback documents will be identified during the trial by asking the NCA clinical audit leads and statistician to record the amount of time taken to perform each of these activities.
- Delivery of the post-feedback support (time of personnel delivering and receiving the post-feedback support session). Project team members delivering the 'post-feedback support' intervention will record the duration and attendance of personnel at the training session provided to each Hospital Transfusion Team. Data on whether hospitals act upon the guidance given and what resources they deploy will be collected as outlined in section 13.5.

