### 10.1 Usual feedback

Current practice is defined as the standard feedback delivered by the NCA following completion of an audit, targeting clinical teams within Trusts or Health Boards. Feedback is typically in the form of a written clinical audit report to hospital sites, a regional PowerPoint presentation and (often) action plan templates. The content of the written report varies, depending on the audit. How these clinical teams and organisations respond following receipt of the feedback is regarded as a consequence of the trial interventions – but is presently considered to be highly variable. We expect them to respond in the context of their clinical governance arrangements. No restrictions will be imposed on current practice or on Trusts or Health Boards undertaking additional development or training in the provision of feedback, with the exception that we will request that the staff who receive the feedback do not share with colleagues external to their own Trust or Health Board.

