| Role of the data collector                                                               |                                 |              | X        | X         |
| Data on Intervention Delivery                                                            |                                 |              |          |           |
| Intervention Fidelity (Design) (WS1→CTRU/WS3)                                            |                                 |              |          | X & Y     |
| Intervention Fidelity (Training) (ID→CTRU/WS3)                                           |                                 |              |          | X & Y     |
| Intervention Fidelity (Delivery)
(IP→CTRU/WS3/Oxford)                                 |                                 |              |          | X & Y     |
| Intervention Fidelity (Receipt)
(HTT→CTRU/WS3/Oxford)                                 |                                 |              |          | X & Y     |
| Intervention Fidelity (Enactment)
(HTT→CTRU/WS3/Oxford)                               |                                 |              |          | X & Y     |
| Contamination Events (NCA, ID, RTC→CTRU)                                                 |                                 |              |          | Z         |
| Unblinding Events (DCo, NCA→CTRU)                                                        |                                 |              |          | Z         |
| Data on intervention costs                                                               |                                 |              |          |           |
| Resource inputs for audit data collection and submission (DCo → NCA→CTRU →UCL)           |                                 |              | X        |           |
| Resource inputs for production and delivery of feedback documents (AL + NCA →CTRU → UCL) |                                 |              | X        |           |
| Resource inputs for 'post-feedback support' intervention (WS1→CTRU → UCL)                |                                 |              | X & Y    |           |

Data Collectors (DCo); SHOT=Serious Hazards of Transfusion database; BSMS=Blood Stocks Management Scheme database; AL=Audit Lead; HTT=Hospital Transfusion Team; ID=Intervention Developers; IP=Intervention Providers; WS1=AFFINITIE Work Stream 1; WS3=AFFINITIE Work Stream 3

X = Mainly quantitative data collected as part of Works Stream 2 by CTRU

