### 13.5 Data on intervention delivery

Data on intervention delivery will be collected by individuals from the central team or from members of the Hospital Transfusion Team (forms to be completed by the HTT are marked with an asterisk as indicated below). Data will be collected on case report forms / online questionnaires / in-built web analytics and forwarded to the CTRU:

Intervention Design:

- Intervention Design and Specification Checklist
- Intervention Provider Selection/Recruitment Checklist (this will include basic characteristics of providers: job title, training, relevant experience).
- Confounder and Implementation Setbacks Monitoring Form

Training:

- Training Delivery Log
- Training Competency Log
- Intervention Provider Selection/Recruitment Checklist

Delivery

- Delivery of Intervention Components Record
- Delivery of telephone support log
- Recipient Toolkit Access Log (Computer Generated; i.e. web analytics data of number of log ins, duration of log in, number of page views, completion of problem solving, goal setting, action planning tools)
- Non-Manual Specified Intervention Content Delivery Record

Receipt

- Intervention Comprehension and receipt Questionnaire\*
- Receipt of NCA Documentation (Computer Generated; i.e. number of feedback report downloads)
- Brief Acceptability Questionnaire\*

Enactment (Enhanced Interventions Only)

- Intervention Enactment Checklist\*
- Enactment of web toolkit log (i.e. web analytics data)

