## **18 Economic evaluation**

### **18.1 Design**

Two cost-effectiveness analyses (one for each trial) will be conducted using decision analytic modelling. Both analyses will be conducted from the perspective of the NHS. To help inform decision making around the future implementation of A&F, the analysis requires a direct comparison of the costs and effects of all four A&F options (conventional A&F, enhanced content only, post-feedback support only, and combined enhanced content and post-feedback support) so as to determine which is likely to be the most cost-effective alternative and offer the best value for money. These works will draw on a variety of data collected specifically during the trial (see section 13 above and section 18.2 below), together with data generated elsewhere within and beyond the AFFINITIE Programme.

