As detailed in section 13.6 above, data will be collected on a small sample of the clinical audit proformas used in the trials on time taken by hospital staff to identify and extract the required audit data during the trials. The time taken to enter these data onto the NCA on-line system will be estimated by members of the research team performing the data entry for a sample of 'mock' audit cases. These data will allow costs of the current NCA audit process to be quantified and will provide data for costing any new re-audits implemented at sites attempting to change behaviour following receipt of the post-feedback support). The resources required to design and populate the standard and enhanced versions of the feedback documents will be identified by asking the NCA clinical audit leads and statistician to record the amount of time required to perform such activities. Project team members delivering the 'post-feedback support' intervention will record the duration and attendance of personnel at the training session provided to each Hospital Transfusion Team. Data on whether hospitals then act upon the guidance given will be collected by a subsequent AFFINITIE work stream (work stream 3). The trials will also provide data on the current rate of unnecessary transfusions and the relative effectiveness of the interventions in reducing this rate for populating the model. Data will also be available via the trials on the volumes of blood components transfused to each audit case so as to estimate the mean number of product units per unnecessary transfusion. The organisational survey conducted at baseline and follow-up will include information on the components of patient blood management conducted at hospitals before and after the audit and will allow identification and costing of increased uptake of patient blood management policies in each trial arm. A combination of data from the published literature, expert clinical opinion, the UK haemovigilance system (Serious Hazards of Transfusion (SHOT)) and the Blood Stocks Management Scheme (BSMS), will be used to estimate the probability, cost, HRQoL, and survival impact of transfusion-related adverse events.

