### **18.3 Analysis**

A lifetime horizon will be used for the analysis and model results for each intervention will be reported as mean discounted costs and a series of outcomes (for example adverse events, life years, and quality adjusted life years). Incremental analyses will compare the costs and effects of each of the interventions versus standard A&F. Structural uncertainty in the model will be examined using sensitivity analysis and the model's internal consistency assessed using extreme value sensitivity analysis. Parameters will be entered into the model as

distributions and probabilistic sensitivity analysis used to assess the impact on the cost-effectiveness results of joint parameter uncertainty.

Cost effectiveness acceptability curves will identify the intervention most likely to be cost-effective for different values of willingness to pay for additional health gain. We shall liaise with the National Comparative Audit Team, SHOT, and NHSBT to ascertain whether any independent data are available to facilitate the external validation of the model.

The general methodology utilised to perform the cost-effectiveness analysis of the A&F interventions here will be described within a health economic analysis plan and will feed into the bank of resources planned for the knowledge exchange phase of the programme.

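### Staff time and re-audits spent responding to feedback are to be collected or costed only for sites given post-feedback support, although incremental costs are taken against standard feedback, whose sites also respond

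*Protocol*

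**What the plan says.** Protocol 13.6 lists three kinds of resource data: audit data collection, production of the feedback documents, and delivery of post-feedback support. What hospitals themselves spend in response appears only under the third: "Data on whether hospitals act upon the guidance given and what resources they deploy will be collected as outlined in section 13.5".

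In 13.5 the forms on acting upon feedback stand under the heading "Enactment (Enhanced Interventions Only" (closing bracket omitted here). Table 1 has a cost row "Resource inputs for 'post-feedback support' intervention", supplied by Work Stream 1, and no row for resources that hospitals use in responding to usual feedback. Section 18.2 says the audit timing data will serve for "costing any new re-audits implemented at sites attempting to change behaviour following receipt of the post-feedback support".

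On the comparator, 10.1 says of usual feedback: "How these clinical teams and organisations respond following receipt of the feedback is regarded as a consequence of the trial interventions". It adds that these responses vary widely, are expected to follow local governance, and are not restricted. Section 18.1 states that "the analysis requires a direct comparison of the costs and effects of all four A&F options", and 18.3 that "Incremental analyses will compare the costs and effects of each of the interventions versus standard A&F".

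**The concern.** A trust that receives the standard report, often with action plan templates, may hold meetings, assign staff and run its own re-audit. If that work is recorded and priced where post-feedback support was given but not elsewhere, the difference in cost between arms contains work that would also have been done without the support. The primary outcome comes from the same follow-up audit in every arm, so effects are measured alike while this cost item is not.

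At stake is one input to the two cost-effectiveness models, and through it the incremental cost of post-feedback support, alone or combined with enhanced documents. The error would run against the supported options.

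**Working it through.** The plan states no figure to reproduce. The check sets the sections side by side and then uses a simple identity.

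**What is available, by arm**

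| Cost component | Usual documents, no support | Enhanced documents only | Post-feedback support (either document type) |
|---|---|---|---|
| D: producing and delivering feedback (13.6, Table 1) | yes | yes | yes |
| P: changed blood management practice (18.2, organisational survey) | yes | yes | yes |
| S, staff time spent responding (13.6, 13.5) | not planned | not under 13.6; enactment forms apply under 13.5 | planned |
| S, re-audits (18.2) | not planned | not planned | planned |

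**Identity.** Let 0 denote an arm without support and 1 an arm with it.

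- True increment = (D1 + P1 + S1) − (D0 + P0 + S0).
- Increment as planned, if S1 is recorded in full and S0 is not recorded = (D1 + P1 + S1) − (D0 + P0).
- As planned minus true = S0.

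So the overstatement equals the response staff time and re-audits of the comparator arm. It is zero only if those sites spend nothing of this kind, which 10.1 does not lead one to expect. P cancels from the error because it is costed on both sides.

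**Which comparisons are touched**

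1. Support alone, or the combined package, against standard feedback: overstated by S0 of the usual arm.
2. Support against enhanced documents only: overstated by whatever part of the documents-only arm's S is not collected. That is the whole of S if 13.6 and 18.2 are followed, and at least the re-audits if the 13.5 forms are also used there.
3. Enhanced documents only against standard feedback: if S is collected in neither arm, the error is minus the difference between the two arms' S. Its sign is not known.

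**Dependence on what the forms record.** Write R for what is actually recorded in a supported arm. The error is then R − (S1 − S0). With R = S1 it is S0. If R covered only the extra work caused by the support, R = S1 − S0 and the error would vanish. The protocol does not describe any form in 13.5 as recording staff hours or numbers of re-audits, so R cannot be pinned down from the text.

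**The case against.** The strongest reply is that usual-arm sites are not left without data.

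- **Practice change is costed everywhere.** Section 18.2 puts changed clinical practice into the model and uses the organisational survey, at baseline and follow-up, to cost policy uptake in each arm. This stands. A reader might infer that usual feedback is costed with no local response at all; the protocol does not support that. The survey as described covers structures, resources and policies, however, not response hours or re-audits.
- **Enactment data are described for all hospitals elsewhere.** Section 12 plans fidelity assessment for enhanced and standard feedback and sends questionnaires covering receipt and enactment to every hospital. Table 1 lists enactment data without restriction by arm. This conflicts with the heading in 13.5, so 13.5 alone does not prove that usual-arm responses go unrecorded. But section 12 describes these data as limited and high-level and names no resource item. The interviews cover all four arms, but only 12 trusts per trial, and they concern barriers, understanding and enactment rather than quantities.
- **The 13.6 item may be narrower than total response.** It concerns guidance that unsupported sites never receive, so it may lie closer to the extra work than to the whole. This is a fair limit on the identity above. The protocol does not say how a supported site would separate the two.
- **The health economic analysis plan is not shown.** It might assign a value to the usual arm. It could do so by assumption or from outside sources, but it cannot recover trial data that were never gathered.

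**Conclusion.** The point holds in a limited form. As written, response staff time and re-audits are planned to be collected or costed only where post-feedback support was given, while increments are taken against standard feedback. To the extent that usual-feedback and documents-only sites incur these costs, the incremental cost of support is overstated by the uncollected amount. This rests on two assumptions: that such sites do spend something in responding, as 10.1 implies, and that the supported arms' response is recorded substantially in full.

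The size cannot be computed from the documents. A reader might attach a multiple. If a usual site spends h hours and a supported site h + d, the recorded increment is 1 + h/d times the true one; assumed values of d at 25%, 50% or 100% of h give factors of 5, 3 or 2. Those ratios are pure assumption and apply to the local-response component alone, not to total incremental cost, which also contains delivery, transfusions avoided, adverse events and changed practice over a lifetime. Nor do the documents show that the ranking of the four options would change. The primary effectiveness analysis is untouched.

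**What to change.** 1. Reconcile section 12 and Table 1 (enactment data from all hospitals) with 13.5 (enhanced interventions only), and state in one place which arms complete which form.
2. Add identically worded items on staff time spent responding, by grade, and on re-audits carried out to the questionnaire already sent to all hospitals about six months after delivery. Ask for total response to the feedback, so that supported sites need not judge what was extra.
3. Amend 13.6 and 18.2 so that these items are costed in all four arms before increments are taken, add a matching row to Table 1, and carry the same wording into the health economic analysis plan.

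The items should be in place before the questionnaire goes out, because later recall of staff time would be poor. The cost is one or two extra items on an existing form and slightly more respondent burden, chiefly in trusts without post-feedback support. No new visit, instrument or patient data are needed. If the items cannot be added, the analysis should state the value assumed for response costs in the unsupported arms and vary it in sensitivity analysis.

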## 13.7 Data Transfer

Data collected on the clinical audit cases and the organisational survey will be obtained via the NCA BT in line with standard agreed processes for conducting a NCA audit.

All electronic data transferred to the CTRU will be in the form of anonymised datasets as specified in the sections above. The CTRU will be able to link data on NHS Organisations across data sources but will not be able to do so for patients. Data Transfer Agreements (including details on the sender, recipient, content of transfer / general purpose of transfer and any data processing limitations) will be set-up between the following organisations prior to the transfer of any data:

- NCA BT and the CTRU
- SHOT and the CTRU
- BSMS and the CTRU
- CTRU and University of Oxford (for the health economics data)
- City University and CTRU (for the process evaluation data)

All data will be provided on the condition that it is stored, handled and processed in accordance with the principles of the 1998 Data Protection Act, the operation of the data transfer agreement and the Study Publication Policy. The rights for this data belong to the Study Sponsor and no processing, including further data transfer in whole or in part to a 3rd party, is permitted other than as stated in the data transfer agreements.

Other data collected (e.g. data collectors, intervention fidelity, contamination / unblind events) will be reported to the CTRU on a paper CRF or electronically in a spreadsheet.

## **14 Withdrawal**

It is possible for the NHS Trust / Health Boards to withdraw NHS Permission (i.e. consent) at any point during either trial after randomisation. NHS Trusts / Health Boards will be able to withdraw from the trial as a whole i.e. 'the intervention and trial data collection' or 'the intervention'. (Note: that this active withdrawal is distinctive from remaining in the allocated arm but not receiving the intervention or parts thereof for other reasons). NHS Trusts / Health Boards will withdraw consent by making contact with the CTRU. They will be asked to give a reason for their decision but are not required to do so if they prefer not to. Any data collected for that NHS Trust / Organisation up to the point of withdrawal would be used in the analysis. NHS Trusts / Organisations will be able to withdraw from one or both of the audit topics.

## **15 Data monitoring, data management & quality**

### **15.1 Monitoring schedule**

A Trial Monitoring Plan will be developed and agreed by the Trial Management Group (TMG) and Trial Steering Committee (TSC) based on the trial risk assessment. This Trial Monitoring Plan will be developed considering the scientific value of the research (including the potential risk associated with the implementation of the intervention and contamination which can, if not monitored and mitigated, affect the integrity and smooth running of this cluster randomised trial). This monitoring plan will detail the timing and content of reports to monitor trial conduct and implementation and adherence with the Consolidated Standards of Reporting Trials (CONSORT) - extension to cluster randomised trials .

The NCA will implement a data management plan to include ongoing checking of data quality and completeness during the clinical audit collections. Details on processes undertaken by the NCA to adhere to their standards for ensuring data quality in clinical audits will be followed. In brief, during the audit periods, the NCA team will monitor the cases audited at each site and will review data received to identify missing and illogical information. This will help maximise the number of cases reported, the completeness and quality of the data and will allow for monitoring the adherence to the list of cases selected for audit. As a minimum this will include:

- Assessing the data received to identify missing or erroneous data items and chasing this with the data collectors at site until they are confirmed as not available, or when the clinical audit closes.

- Checking for data input errors where data is transferred from paper to the online system at the NCA.
- Monitoring the number of audit cases started at each site and chasing the data collectors at site if progress is not as expected.

Data provided to the CTRU will be monitored for quality and completeness by the CTRU, using verification, validation and checking processes as appropriate. Data will be queried with the source where possible.

